#### 9.5. Pass/fail criteria

Pass: The study group randomized to the online vestibular rehabilitation scores mean  $\geq 3$  VSS-SF points lower compared with the standard care group at 6 weeks.

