## 2.2. Intended purpose

The online vestibular rehabilitation tool (device) is a software intended for use with common handheld devices and computers/laptops to facilitate training/rehabilitation during chronic vertigo without ICD diagnostic limitations (as validated in previous studies, references 10, 11, 13) and after acute onset vertigo (as validated during this clinical investigation). Any diagnosis with dizziness or vertigo as a presenting symptom, including vestibular neuritis, cerebrovascular disease, Meniere's disease, inner ear infections or other disturbances, and more, may present according to the inclusion criteria. However, acutely presenting BPPV patients will not be sought to be included in the investigation and thus not in the intended purpose, as these patients will benefit more appropriately from specific repositioning maneuvers. During the clinical investigation persons with acute onset vertigo (Acute Vestibular Syndrome, AVS) as specified in the inclusion criteria will be targeted for inclusion. As the device (in English and Dutch) has been found effective for use among chronic dizziness patients as well the intended purpose after study completion (if the primary endpoint is met) will be all dizziness/vertigo patients in need of vestibular rehabilitation.

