### 9.3. Analytical procedures

Two-sided statistical tests will always be performed. The primary outcome will be analyzed using analysis of covariance (ANCOVA) adjusting for baseline measurements; known predictors of the outcome including diagnostic group, sex, age and baseline symptom intensity in order to gain precision in treatment effect estimates; and inclusion of a random effect for site to control for influence from stratified randomization. The primary endpoint results will be reported as the ANCOVA generated adjusted VSS-SF difference with 95% CI and p-value between the study arms at 6 weeks. The VSS-SF has previously been analyzed in a randomized trial assuming normality. If a clear deviation from normality is detected an ordinal logistic regression ANCOVA will be used for the primary outcome.

For secondary outcomes with repeated measurements we will use linear mixed models analysis for continuous outcome variables and binary logistic mixed effects models for binary outcome variables with random effects for individual and site. These techniques can account for repeated measures within an individual and unbalances from missing data. The intervention effect will be modelled using a time by intervention interaction term.

We will also perform statistical validation of the Swedish translation of the VSS-SF questionnaire, including analyses of reliability (test-retest reliability and internal consistency reliability) and validity; construct validity (convergent and discriminant validity) by investigating item-to-item associations between VSS-SF/VSS-SF domains and DHI; and criterion validity by correlating the domains to DHI and balance tests. For the test-retest

study, the first 100 included subjects will complete the evaluator-blinded 6-week assessments of VSS-SF twice, 48 hours apart, via telephone .

Ranked analysis of covariance (ANCOVA) will be used to evaluate intervention effects on T25-FW and VOR gain and saccades, as this method provides robust estimates even though there may be extreme outliers in skewed data. The percentage of participants with sustained improvement in VSS-SF defined as  $\geq 3$  points improvement at 6 weeks and 3 months will also be compared using binary logistic regression.

We will report crude and adjusted analyses, adjusting for baseline values of the studied outcome and the prespecified predictors sex, age, level of education, number of chronic diseases and baseline AVS etiology.

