#### 9.4. Sample size calculation

A change in VSS-SF score of 3 or more has been defined as clinically significant. In an earlier study on a Dutch version of the online vestibular rehabilitation tool on primary care chronic dizziness patients the mean VSS-SF score at three months in the intervention group was 8.1 (SD 7.4), and in the control group 11.5 (SD 9.9). In order to detect a difference in VSS-SF score of 3, assuming a standard deviation of 9 and a correlation between pre and post measurements of 0.6 with 90% power, alpha 5%, we would need n=156 participants, 78 in each arm, using the Shieh sample size calculation method implemented into the Superpower package. Assuming a 15% drop out rate the sample size needs to be increased to n=184 to preserve power. Conservative observational data suggest a yearly incidence of 36 patients with acute onset vertigo and nystagmus per 100,000 inhabitants in the Umeå University uptake area.

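### The pass threshold equals the design effect, so the stated 90% power is not the chance of passing, which is 50% at a true difference of 3 points

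*Protocol*

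**What the plan says.** Section 9.5 holds the protocol's only pass definition. It reads "The study group randomized to the online vestibular rehabilitation scores mean" at least 3 "VSS-SF points lower compared with the standard care group at 6 weeks". It sets no p-value or confidence-interval condition and does not mention the primary analysis.

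Section 9.4 sizes the trial "In order to detect a difference in VSS-SF score of 3". The other inputs there are an SD of 9, a pre/post correlation of 0.6, power of 90% and a 5% alpha. This gives 78 per arm, and 184 enrolled after 15% dropout.

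Section 9.3 makes all tests two-sided. It says that the primary results "will be reported as the ANCOVA generated adjusted VSS-SF difference with 95% CI and p-value between the study arms at 6 weeks". Section 5.2 labels the primary objective as superiority.

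Two other sections attach consequences to the result. Section 2.2 says that "the intended purpose after study completion (if the primary endpoint is met) will be all dizziness/vertigo patients in need of vestibular rehabilitation". Section 13 makes wider release of the tool depend on a positive primary endpoint. Neither refers to section 9.5.

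**The concern.** The protocol contains two success rules and does not connect them. One is the superiority test of zero difference, which is what a sample size with power and alpha is built for. The other is a threshold on the observed mean difference, set at exactly the difference the sample size assumes. A reader of sections 9.4 and 9.5 together would take 90% as the chance of passing if the tool truly gains 3 points. That is not so.

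The rules can also disagree on the same data. An adjusted difference of 2.6 points with p below 0.05 would be superiority under section 9.3 and a failure under 9.5. In a pivotal confirmatory investigation (section 3.3), the conditions in sections 2.2 and 13 would then have no agreed answer.

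**Working it through.** **Inputs.** Pass threshold 3 (section 9.5). Design difference 3, SD 9, pre/post correlation 0.6, power 90%, alpha 5%, 78 per arm, dropout 15% (section 9.4). Two-sided testing (section 9.3). Earlier study: 11.5 − 8.1 = 3.4 points (section 9.4).

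**Step 1: the plan's own figure.** The dropout step reproduces: 156/0.85 = 183.5, so 184. The 78 per arm depends on how 0.6 is read.
- As a correlation, the residual SD is 9 × √(1 − 0.6²) = 7.2. The Shieh ANCOVA method then needs 123 per arm, and 78 per arm gives about 73% power (74% by normal approximation).
- As R-squared, the residual SD is 9 × √(1 − 0.6) = 5.69. The same method gives exactly 78 per arm, with power 90.3%.

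This discrepancy is a separate matter. Here it means only that both residual SDs are carried through.

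**Step 2: formulas.** SE = residual SD × √(2/78). Chance of passing at a true difference d = Φ((d − 3)/SE). True difference for a 90% pass chance = 3 + 1.2816 × SE. Smallest significant difference = 1.96 × SE.

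| Quantity, 78 per arm | Residual SD 5.69 | Residual SD 7.2 |
|---|---|---|
| SE | 0.911 | 1.153 |
| Chance of passing, true difference 3 | 50% | 50% |
| Chance of passing, true difference 3.4 | 67% | 64% |
| True difference for 90% chance of passing | 4.17 | 4.48 |
| Smallest significant difference | 1.79 | 2.26 |
| Power of the two-sided test at 3 (normal approximation) | 91% | 74% |
| Significant but fail, true difference 3 (power − 50%) | 41% | 24% |
| Chance of passing, no true effect | 0.05% | 0.46% |

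The 50% row needs no SD or n: when d = 3 the argument of Φ is zero. With 92 per arm the chance at 3.4 is 68% or 65%, and the difference for 90% is 4.08 or 4.36.

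**Step 3: source of the 50%.** Adding p < 0.05 to the rule leaves it at 50%. Under both residual SDs every estimate of 3 or more is already significant, because 1.79 and 2.26 lie below 3.

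**Step 4: can a non-significant result pass?** That needs SE above 3/1.96 = 1.53, so a residual SD above 1.53/√(2/78), about 9.6. The planned SD is 9 before any adjustment. With no gain from adjustment at all (residual SD 9), the smallest significant difference is 2.82 and the chance of passing with no true effect is 1.9%. That is still under the 2.5% in the favourable tail of the two-sided test.

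**The case against.** The best defence is that requiring an observed gain of clinically relevant size is a legitimate and demanding criterion, and the choice belongs to the sponsor. A rule based on significance alone would let about 1.8 to 2.3 points pass, less than the change the protocol calls clinically significant. This stands. The threshold is not wrong in itself; the fault is that the 90% in section 9.4 is not said to describe the test rather than passing. It is also fair that 50% is the figure at the design difference, and that the only earlier estimate in the protocol, 3.4, gives 64% to 67%.

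A reader might infer several stronger points, which the protocol does not support:
- *The missing significance condition causes the 50%.* It does not; the cause is that the threshold equals the design effect (step 3).
- *The rule conflicts with the test in both directions, or inflates false positives.* Under the planned SDs only one direction occurs, significant but fail (step 4).
- *The deciding estimate is undefined.* Section 9.3 names the adjusted ANCOVA difference as the primary result. The later list with "the prespecified predictors sex, age, level of education, number of chronic diseases and baseline AVS etiology" follows the paragraphs on secondary outcomes and can be read as general reporting. Section 9.5 lacks only the word adjusted and a cross-reference.
- *Section 9.5 decides the release of the tool.* Sections 2.2 and 13 do not cite it. They may equally mean the significance test, and that ambiguity is the accurate criticism.
- *The 3 points are invalid between groups because section 6.3 describes a change from baseline.* That is a different question. It rests on cited sources that are not at hand and does not affect the calculation.

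**Conclusion.** The point holds as a conflict between sections 9.4, 9.3 and 9.5. The stated 90% power applies at most to the two-sided test of zero difference. The chance of passing is 50% at a true difference of 3. With 78 per arm it is about 64% to 67% at 3.4, and a true difference of about 4.2 to 4.5 is needed for 90%. Observed differences from about 1.8 (residual SD 5.69) or 2.3 (residual SD 7.2) up to 3 would be significant yet fail. If the truth is 3, that outcome has a probability of about 41% or 24% respectively.

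The 50% assumes only an unbiased, symmetrically distributed estimate. The other figures also assume approximate normality, 78 evaluable per arm and one of the two residual SDs, without further gain or loss from the other covariates or the site effect. The rule is stricter than the test, so the risk is an unclear or unintended failure, not a false success.

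**What to change.** Reconcile section 9.5 with section 9.3 in one of two ways.

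- **(a)** Define pass as the 95% CI of the adjusted VSS-SF difference at 6 weeks excluding zero in favour of the online tool. Take the difference from the primary intention-to-treat ANCOVA with the covariates in the first paragraph of section 9.3. Report separately, as clinical relevance, how the estimate and its CI compare with 3 points.
- **(b)** Keep the 3-point condition but place it on that same adjusted estimate. State in section 9.4 that the 90% power refers to the significance test only and that the chance of passing is 50% at a true difference of 3.

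Under either option, say in sections 2.2 and 13 that a met or positive primary endpoint means the chosen rule. Section 9.3 also allows an ordinal logistic model if normality clearly fails. That model gives no difference in points, so one clause should say what decides in that case.

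The cost is a rewritten section 9.5, a sentence in section 9.4 under option (b), and short cross-references. Data collection, sample size and conduct do not change. The change should be made, through the amendment route in section 11, before anyone sees the 6-week results by arm.

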#### 9.6. Interim analysis

An interim drop-out rate analysis performed on 25th April 2023 after 138 included subjects (of which 129 have reached 6 weeks) supports the initial drop-out rate assumptions.

#### 9.7. Multiplicity control

No adjustment for multiplicity will be performed as the study has only one primary endpoint.

## 9.8. Subgroup analysis

Subgroup analyses will be performed by assessing for interaction by:

- a) baseline diagnostic group (categorical), i.e., unilateral vestibular deficit (most often vestibular neuritis), cerebrovascular vertigo (stroke) and vertigo NOS.
- b) sex (categorical)
- c) age (continuous)
- d) study site (categorical)
- e) baseline symptom severity – VSS-SF (continuous)
- f) BPPV diagnosis or not at 3 months (categorical)

## 9.9. Missing data

To preserve the ITT principle for the primary endpoint we will use, hierarchically, (1) the 6 weeks assessment of VSS-SF; if missing, (2) the 3 weeks assessment; and (3) the 3 months assessment. A sensitivity analysis will be performed by comparing the primary analysis results with and without the imputed values from the 3 weeks and 3 months values.

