| Compare the effect of online vestibular rehabilitation with standard written instructions after acute onset vertigo on vestibular symptoms (superiority).                                                                                                                                                                                                                                                                                                                                                                                                                                                                                                                                                                                                                                                                                                                                                                                                                                                                                                                                                                                                                                                                                                                                   | The vertigo symptom scale short form (VSS-SF) score at 6 weeks after vertigo onset.                                                                                                                                                                                                                                                                                                                                                                                                                                                                                                                                                                                                                                                                                                                                                                                                                                                                                                                                                                                                                                                                                                                                                 |

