## 6.2. Measurements to minimize bias

Subjects will be block-randomized (random blocksize of 4, 6 and 8) 1:1 using site-specific randomization lists generated in R. Randomization will be performed by an independent statistician at Registercentrum Norr. As a precaution measure the lists will contain 4 times as many posts as the expected number of participants at each site. The treatment allocation will be open to the participants and to the site study coordinators, however blinded primary endpoint assessments at week 6 by study coordinators from surrounding sites will be performed as detailed below (section 6.7).

To minimize the risk for an increased effect of rehabilitation mediated by the increased motivation stemming from participating in a clinical trial (in both study arms) the study nurses will be instructed to try to avoid acting as “coaches” and instead concentrate on data collection at the contacts with the participants. This way the effect in the intervention arm will be isolated to the vestibular rehabilitation app, and the effect in the control arm will be isolated to mimic current clinical practice.

Sites will differ according to patient base (e.g., ENT outpatient clinics vs stroke wards). This will entail site mediated differences in participant characteristics. Bias stemming from these differences will be mitigated by including a random effect for site in the primary outcome analysis, and by site stratified randomization.

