## 6.3. Measurement of variables

The VSS-SF measures the frequency of 15 vestibular symptoms on a scale from 0 (no symptoms) to 4 (symptoms most days) during the past month. The score range is 0–60 and a difference from baseline of  $\geq 3$  points indicate a clinically significant change. The time frame (1 month) for the symptoms will be left as is for the evaluations at week 6 and after 3 months but for the baseline measurement the participants will be asked to report their symptoms during the last 24 hours; and the two response alternatives indicating the highest frequencies (3, quite often [every week] and 4, very often [almost every day]) will be modified to: 3, quite often (almost every hour) and 4, very often (almost all the time). Although this is a deviation from the original version of the VSS-SF this modification is necessary to capture the short-term status of participants soon after vertigo onset. The modified VSS-SF data will be used for the baseline symptom intensity assessments only.

The DHI (range 0–100 points, 0–30 mild, 31–60 moderate and  $\geq 61$  severe dizziness) investigates the effects of dizziness on everyday living. The between group mean DHI score will be compared at each time point as detailed in the statistics section. The scale has subcategories (physical, emotional and functional for DHI) and these will be analyzed separately as exploratory analyses although the total scores will be used for the secondary outcomes.

EQ-5D is an generic instrument which consists of five sub-domains (mobility, self-care, usual activities, pain/discomfort and anxiety/depression) with three severity levels (no, moderate and severe problems). For the current study, the Swedish version EQ-5D-3L will be applied, and the Swedish value set based on experienced health states will be applied to

obtain a health utility score in order to calculate quality-adjusted life years (QALYs). The UK MvH value set will be applied for sensitivity analyses.

The T25-FW data will be collected by using the mean (seconds) of two, timed attempts at walking a clearly marked 25-foot course.

Basic body sway data will be collected by using a locally developed application which utilizes cell phone built-in motion tracking. An enhanced gait analysis with a wearable motion tracking system will be performed at Umeå University Hospital for in-depth measurements.

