#### 6.6.4. Unblinding

The clinical investigation is only blinded for the evaluators at week 6 and for the statistical analyses. Therefore, no emergency code breaking protocol is needed.

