weekly online sessions consist of educational texts, symptom control techniques, scoring tests and exercise prescriptions for the following week. The exercises for the following week after each online session will be adapted to the user and thus become successively more difficult if the user scores lower discomfort during evaluations, or the opposite if the user scores higher discomfort. There are 6 different exercises in the tool: 1. Head shake with open eyes, gaze following the head; 2. Head nod with open eyes, gaze following the head; 3. Head shake with closed eyes; 4. Head nod with closed eyes; 5. Head shake with open eyes, gaze fixated and; 6. Head nod with open eyes, gaze fixated. These exercises are performed sitting, standing and walking depending on symptom intensity. There are 4 symptom control techniques in the tool in order to deal with secondary anxiety issues related to the vertigo: 1. Controlled breathing; 2. Relaxation; 3. Stress management and; 4. Thought control.

Control: After randomization written instructions with the 6 different exercises from the online rehabilitation tool is handed out and the participant is instructed to increase difficulty if possible. Participants are also given general advice to prevent inactivity and secondary dizziness and fear of motion. Data collection as for the intervention arm. At the end of the core study at 3 months from randomization the standard care study arm participants will also be granted access to the online rehabilitation tool and followed until 12 months.

The Swedish translations of VSS-SF, DHI, and EQ-5D-3L are collected locally at all sites by the site study coordinator. These questionnaire data will be collected by in-person interview at day 0, week 6 and after 3 months, except for VSS-SF at 6 weeks (primary endpoint) which will be collected by phone call interview by a blinded study coordinator at either the same site or a different site. In the case of the first 100 included subjects, the VSS-SF at 6 weeks (primary endpoint) will be collected by phone call interview twice, 48 hours apart, as part of the statistical validation of the Swedish translation of the VSS-SF questionnaire. Also, at week 3 and after 12 months VSS-SF and EQ-5D data will be collected by phone call interview (figure 1).

The T25-FW data will be collected by letting the subject walk a clearly marked 25-foot course during follow-up appointments at each site.

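### Filling a missing 6-week VSS-SF with the week-3 or month-3 score inside the primary analysis can bias the 6-week difference

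*Protocol*

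**What the plan says.** The primary endpoint (section 5.2) is "The vertigo symptom scale short form (VSS-SF) score at 6 weeks after vertigo onset", and section 9.5 sets the pass mark at a mean at least 3 points lower at that time. Section 9.3 analyses it by ANCOVA with a random effect for site.

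For a missing value, section 9.9 uses, in order, "1) the 6 weeks assessment of VSS-SF; if missing, (2) the 3 weeks assessment; and (3) the 3 months assessment". It adds one check: "A sensitivity analysis will be performed by comparing the primary analysis results with and without the imputed values".

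On blinding, section 6.2 states: "The treatment allocation will be open to the participants and to the site study coordinators". The 6-week score is "collected by phone call interview by a blinded study coordinator at either the same site or a different site" (section 6.7), and section 6.6.4 says: "The clinical investigation is only blinded for the evaluators at week 6 and for the statistical analyses".

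On recall, section 6.3 states: "The time frame (1 month) for the symptoms will be left as is for the evaluations at week 6 and after 3 months". The modified 24-hour form is reserved for baseline. Week 3 is not named.

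For secondary outcomes with repeated measurements, section 9.3 chooses mixed models with a time-by-intervention term, on the ground that "These techniques can account for repeated measures within an individual and unbalances from missing data".

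**The concern.** The rule treats scores from three visits as interchangeable in a condition where recovery is expected. Nothing else in the protocol does so: Table 2 lists the VSS-SF comparisons at week 3, week 6 and month 3 separately, and section 5.3 expects recovery to be faster as well as greater, so a constant effect over time is not assumed.

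The substitutes differ from a 6-week score in three ways.

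- **Timing.** Week 3 is half way through a 6-week programme. Month 3 is well after it ends.
- **Recall.** By implication the one-month form applies at week 3. Inclusion is within 7 days of onset and the contact is at day 21 ± 3, so it falls at most 18 to 31 days after onset and the recall period reaches back to, or close to, the acute phase. At day 42 ± 3 the recall period starts after the first week.
- **Blinding and mode.** Blinding is planned only at week 6. Month 3 is also collected in person, whereas week 6 is by phone.

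If the effect or the mean level differs between visits, the estimate is a blend and not a 6-week difference. The sample size is planned for a difference of 3 (section 9.4), which is also the pass mark, so shifts of a few tenths of a point matter.

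**Working it through.** **The protocol's own figure.** Section 9.4 allows 15% dropout: 156 / 0.85 = 183.5, rounded up to 184. Then 0.15 × 184 = 27.6, so at most about 28 participants, some 14 per arm, would need a substitute. The protocol gives no figure for the effect of the rule, no VSS-SF time course and no dropout by arm.

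**Assumptions (not in the protocol).** True benefit d6 = 3.0 at week 6 and d3 = 1.5 at week 3; control mean falls G = 5 points from week 3 to week 6; missingness is unrelated to outcome within arm; every missing case has a week-3 score.

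**Formula.** With missing fractions mt (intervention) and mc (control), the expected benefit after substitution is

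E = (1 − mt) × d6 + mt × d3 + (mc − mt) × G

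| Missing, intervention / control | Calculation | E |
|---|---|---|
| 15% / 15% | 0.85 × 3 + 0.15 × 1.5 + 0 | 2.78 |
| 20% / 10% | 0.80 × 3 + 0.20 × 1.5 − 0.10 × 5 | 2.20 |
| 10% / 20% | 0.90 × 3 + 0.10 × 1.5 + 0.10 × 5 | 3.35 |

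**Range over the assumptions.** With 15% missing in both arms, week-3 effects of 0, 1, 2 and 3 give 2.55, 2.70, 2.85 and 3.00. The last is the no-bias case. With 20% / 10%, a fall G of 3 to 8 points gives 2.40 to 1.90; with 10% / 20% it gives 3.15 to 3.65.

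**If only half of the missing cases have a week-3 score** and the rest have nothing to substitute, the substituted share of the analysed participants is f = (m/2) / (1 − m/2): 0.081 for 15%, 0.111 for 20%, 0.053 for 10%. Then:

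- 15% / 15%: 3 − 0.081 × 1.5 = 2.88
- 20% / 10%: 3 − 0.111 × 1.5 − (0.111 − 0.053) × 5 = 2.54
- 10% / 20%: 3 − 0.053 × 1.5 + (0.111 − 0.053) × 5 = 3.21

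The bias shrinks by about 40 to 45%.

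**Simulation** (4,000 trials, 92 per arm, SD 9 and correlation 0.6 from section 9.4, ANCOVA on baseline; 5% of week-3 scores also missing, with month 3 then used where available). The repeated-measures-type estimate regresses week 6 on arm, baseline and week 3.

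| Scenario | Substitution | Observed week 6 only | Repeated-measures type |
|---|---|---|---|
| 15% / 15% | 2.80 | 3.01 | 3.01 |
| 15% / 15%, d3 = 3 | 3.00 | 2.99 | 2.99 |
| 20% / 10% | 2.24 | 2.97 | 2.98 |
| 10% / 20% | 3.34 | 3.00 | 3.00 |
| 20% / 10%, missingness depends on week-3 score | 2.12 | 3.10 | 2.98 |
| 10% / 20%, missingness depends on week-3 score | 3.55 | 2.83 | 2.98 |

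With no true effect and 10% / 20% missing, substitution yields a false benefit of 0.46 (type I error 6.7%) for a fall of 5 points and 0.75 (11.0%) for a fall of 8. With 15% / 15% missing and no effect, type I error is 4.9%.

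**The case against.** The strongest reply is that section 9.9 already plans a comparison with and without the substituted values, which in effect gives the observed 6-week analysis. In the simulation that estimate is unbiased when missingness is unrelated to outcome within arm. So a shift would be seen, and the dispute is about which analysis comes first. That stands, with two limits: the substituted result remains the one judged against the pass mark, and the observed-only alternative drifts (3.10 and 2.83 above) when missingness depends on the week-3 score.

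Four stronger readings are tempting and should not be drawn.

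- **That the rule necessarily biases the result.** The documents give neither the time course nor dropout by arm. Section 9.6 says only that overall dropout supports the assumption. A 2:1 ratio between arms is a scenario, not an expectation.
- **That 15% of primary outcomes will sit on the wrong visit.** That is a ceiling: participants lost before week 3 who do not return have nothing to substitute.
- **That the standard error is understated because substitutes enter as observed.** They are real measurements of the participant. In simulation at 15% / 15%, the empirical SD of the estimate was 1.13 to 1.14 against a model standard error of 1.11, which is no material gap.
- **That a mixed model would restore blinding.** It uses the same week-3 and month-3 scores, and participants report the VSS-SF knowing their allocation at every visit. That week 3 is unblinded is also inferred from sections 6.2, 6.6.4 and 6.7; no section says who makes that call.

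An unseen statistical analysis plan does not answer the point, because the protocol itself fixes the rule.

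**Conclusion.** The point holds as a risk of bias built into the primary analysis. Direction and size depend on facts that the protocol does not supply: dilution if the week-3 effect is smaller than the week-6 effect, a shift either way if missingness differs by arm, and none if missingness is equal and the effect constant. Under the stated assumptions the shift is about −0.2 points with equal 15% missingness, −0.8 at 20% / 10% and +0.35 at 10% / 20%, each reduced by roughly two fifths or somewhat more if only half of the missing cases have a week-3 score. Against a 3-point pass mark in a study that section 3.3 calls pivotal and confirmatory, this is worth correcting. It does not invalidate the design.

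**What to change.** In sections 9.3 and 9.9, make the primary analysis a repeated-measures mixed model of VSS-SF at week 3, week 6 and month 3. Include visit, arm, arm-by-visit, baseline VSS-SF and the section 9.3 primary-model covariates each by visit, a site effect and an unstructured covariance within participant. Report the week-6 contrast with its 95% CI and p-value as the primary result. Each score then counts at its own time point. Keep the hierarchical substitution and the ANCOVA on observed 6-week scores as sensitivity analyses. State how the ordinal-regression fallback for clear non-normality carries over to the repeated-measures setting.

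The cost is wording and a little more modelling; the schedule of events already collects every score needed. The model relies on data being missing at random. It does not blind the week-3 and month-3 scores, and it does not resolve the data stopped after recurrence of an acute vestibular syndrome within 6 weeks (section 6.6.3), so that source of missingness should be reported by arm.
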